#### Adherence to treatment

Number of weeks the patient gets pharmacological treatment prescribed by their doctor or nurse, as recorded by the professional in the DCN during each visit or automatically registered by the chat-bot.

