#### Secondary objectives

To assess the intervention effectiveness compared to usual practice as measured through self-reported continuous abstinence at 6 months.To assess the intervention effectiveness compared to usual practice in terms of the improvement in their quality of life measured by the EuroQol-5D-5 L questionnaire.To evaluate the cost-utility ratio of the intervention compared to usual practice in primary healthcare.To assess the intervention effectiveness in terms of improved adherence to pharmacological treatment for tobacco cessation.

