#### Recruitment

Each healthcare professional will select patients who smoke, attend the health center for any reason within the recruitment period, and meet the inclusion criteria. They will inform patients about the characteristics of the trial and offer them to participate. Those who accept will be asked to provide informed written consent. In case they decline, their gender, age, and reason for declining will be recorded.

Various strategies will be implemented in order to increase adherence to the protocol by participating researchers, such us personal follow-up upon achievement of protocol objectives and acknowledgement of their effort via e-mail, and offers of certified training sessions.

Randomized allocation: Subjects will be allocated into the intervention or control group by simple randomization using a software installed in the data collection notebook (DCN). This will be done following the inclusion of patients and data collection in the DCN at the initial visit, which guarantees the masking of the randomization sequence to the professionals recruiting patients. The group assigned to the chat-bot will be the intervention group and those treated with usual care by their doctor or nurse will be the control group.

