### Intervention group

Patients assigned to the intervention group will use a chat-bot whose script for the smoking cessation process has been developed using contents based on current evidence. Subjects will download a messaging application on their smartphone for this purpose and will access the chat-bot with an assigned personal password. The chat-bot will guide them through all the stages of the dishabituation process. The chat is bidirectional, employs multiple media formats, and provides patients with automatic, science-based advice on cognitive-behavioral, motivational, relapse-preventative, and problem-solving techniques. This will take place with different periodicity depending on the quit date and other characteristics of the patient (personal choice, type of tobacco use, personal risk situation, prescribed medication, abstinence-related symptoms, and the evolution of coping with abstinence). The chat-bot also offers information about useful medication to quit smoking prescribed by their healthcare professional, and will recommend how to face problems related to the cessation process through advice and relaxation exercises available in different formats, such as video, computer graphics, games, and web links. Additionally, the chat-bot incorporates gamification elements (games for adults for acquiring new knowledge and skills), including a system to earn scores and badges that will provide access to specific information depending on the abstinence period and the needs of the individual. Specific aspects of the game mechanics (score, levels for different abstinence periods) and dynamics (rewards, acknowledgment) will be developed. Contact with the patient will begin at day ^− 15^, where the above-mentioned strategies will be established, and daily interactive appointments will be set until the quit date. From this point, subjects will receive encouragement and acknowledgement messages that will be spaced out gradually until six months of abstinence. The patient can contact the chat-bot at any time, so the number and total time of interactions are a priori unknown and will be recorded as secondary variables. In terms of proactive contacts, the patient can choose their timing and frequency.

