#### Control group

Patients assigned to the control group will receive the usual practice for smoking cessation, namely the different interventions by primary care nurses and physicians included in the services portfolio of the Madrid Regional Health Service (Service 415, Care for adult smokers) that consist of one or two visits prior to the quit date, follow-up visits after one week and one month, and subsequent control visits depending on whether the opportunity arises, the professional’s criteria, and the patient’s needs.

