#### Variables

The collaborating healthcare professionals will deliver their data prior to the beginning of the study. The recruiting participants will record patient data and will be also responsible for their follow-up. All the information will be recorded on a form created for the trial (DCN). Each collaborator will access the form from their personal computer via the project’s website, using a code for personal identification. Two visits have been defined for data collection of patients: basal and at 6 months.

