## Discussion

Both the healthcare professionals accepting to participate in a clinical trial and the recruited patients may be more interested in the subject of the trial, sharing an increased awareness and motivation for the studied health issues, which can lead to a bias. Although this can result in better outcomes compared to trials with less selective recruiting processes, it would have a conservative effect (namely, it would decrease the magnitude of the intergroup difference).

Additionally, participating collaborators may modify or improve their prescribing habits due to their awareness of being under observation (known as the Hawthorne effect). This may reduce differences between the intervention and control groups in terms of suitability of prescription.

A design by clusters was not chosen in this intervention, since the possible influence among smokers in the same healthcare center would be residual given that the app is personal and with a restricted access for the patient. This circumvents other biases resulting from variability in the clinical practice of included professionals and their basal knowledge on the subject of the intervention.

The intervention cannot be masked, so a blinded evaluation of the main outcome variable has been designed. The researchers in charge of the data analysis and interpretation will be unaware of the allocation arm of patients.

Although the assessment of the effect of the intervention on quality of life is not confirmatory and the expected changes are limited given the short period of time of the trial, we consider it essential to include this outcome variable in the analysis since intergroup differences can be detected even if they are not strongly significant. Additionally, measuring changes in quality of life allows for incorporating outcome variables that are self-reported by the patients, which facilitates the calculation of utilities in the cost-utility analysis. This will enable to overcome some deficiencies and limitations observed in previous interventions by Patterson et al. [24].

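### Medication adherence may be recorded by an instrument that only the chat-bot arm has, and no common measure is fixed, so the adherence comparison is open to ascertainment bias

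*Protocol article*

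**What the plan says.** All references are to the protocol article.

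- **Secondary objectives** list adherence as a measure of effect: "To assess the intervention effectiveness in terms of improved adherence to pharmacological treatment for tobacco cessation".
- **Adherence to treatment** defines the variable as the number of weeks of prescribed pharmacological treatment, "as recorded by the professional in the DCN during each visit or automatically registered by the chat-bot".
- **Recruitment** gives the chat-bot to the intervention group only; controls have usual care. The **Discussion** adds that "the app is personal and with a restricted access for the patient".
- **Intervention group** describes frequent contact: "daily interactive appointments will be set until the quit date", then "encouragement and acknowledgement messages that will be spaced out gradually until six months of abstinence". The patient may also contact the chat-bot at any time.
- **Control group** describes one or two visits before the quit date, then "follow-up visits after one week and one month, and subsequent control visits depending on whether the opportunity arises", the professional's judgement and the patient's needs.
- **Variables** states, without distinction by arm: "Two visits have been defined for data collection of patients: basal and at 6 months".

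**The concern.** A between-arm comparison needs an outcome that is captured in the same way, with the same chance of being captured, in both arms. Here one of the two named sources cannot exist for any control patient. The other depends on visits, and in the control arm these have no fixed date between one month and six months. Medication taken after month one could be logged in the chat-bot arm and missed in the control arm.

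The stake is the fourth secondary objective and the mechanism built on it. The Discussion expects the chat-bot's reminders and monitoring to improve adherence and, through it, abstinence. The component expected to raise adherence is thus also one of the instruments that measures it, and a difference produced by recording could be read as support for the mechanism.

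Randomisation and blinded analysts do not correct unequal capture, and the carbon monoxide check protects only the primary outcome. Replacing missing information with baseline values (Main effectiveness analysis) does not help either, because weeks on treatment has no meaningful baseline value.

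**Working it through.** **1. The plan's own figures.** The article gives no expected weeks, SD or difference for adherence, so there is no adherence figure to reproduce. The only design figure is the primary sample size. With 9.6% against 19.2%, two-sided 5%, 80% power and a pooled variance without continuity correction, n = 209 per arm, or 418, as stated. Adding 10% gives 418 × 1.10 = 459.8, rounded to 460. This does not bear on the point, except that 230 per arm is used below.

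**2. Sources and opportunities by arm.**

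| | Intervention | Control |
|---|---|---|
| Automatic chat-bot record | possible | impossible |
| Professional entry at a visit | possible | possible |
| Contact up to the quit date | daily appointments by chat-bot | one or two visits |
| Contact after the quit date | messages spaced out to six months, plus contact at will | one week, one month, then opportunistic |
| 6-month data visit | yes | yes |
| Adherence tied to the 6-month visit | not stated | not stated |
| Precedence if both sources exist | not stated | not applicable |

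The rows differ by arm everywhere except professional entry and the 6-month visit. That visit is the only defined post-baseline data point common to both arms, and the definition does not name it.

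**3. Illustration of size (all inputs assumed).** True use T is the same in both arms: exponential with mean 8 weeks, capped at 12. A patient without a later record is known only to week 4.

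- Mean if fully recorded: 8 × (1 − e^(−12/8)) = 8 × 0.7769 = 6.21 weeks.
- Mean if known only to week 4: 8 × (1 − e^(−4/8)) = 8 × 0.3935 = 3.15 weeks.
- Shortfall per affected patient: 6.21 − 3.15, about 3.07 weeks.
- Spurious difference (intervention minus control) = 3.07 × (s_C − s_I), where s_C and s_I are the shares without a later record in control and intervention.

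With s_I = 0, 230 per arm, a t-test and 2,000 simulated trials:

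| s_C | Spurious difference (weeks) | False-positive rate (nominal 5%) |
|---|---|---|
| 0 | 0.0 | about 6% |
| 10% | 0.3 | about 12% |
| 20% | 0.6 | about 36% |
| 30% | 0.9 | about 67% |
| 50% | 1.5 | about 99% |

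The sign follows s_C − s_I. With s_C = 10% and s_I = 30%, the same formula gives 3.07 × (−0.20) = −0.6 weeks, against the chat-bot.

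**4. Sensitivity to the SD (also assumed).** If controls are under-recorded by 0.5, 1 or 2 weeks on average and there is no true difference, the chance of a significant result with 230 per arm is:

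- SD 3 weeks: 43%, 95%, about 100%
- SD 4 weeks: 27%, 77%, about 100%
- SD 5 weeks: 19%, 57%, 99%

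A shortfall of half a week is enough to matter at this sample size.

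**The case against.** The best defence is the 6-month visit. It is defined for all patients, and the adherence variable is to be recorded at each visit, which on a plain reading includes that one. A control patient who attends could have all weeks of use entered then. If every control has such a record, the illustration gives no bias. If only the planned 10% losses lack one, it gives about 0.3 weeks. It can also be said that this is one sentence in a condensed article, and that notebook fields and source precedence may sit in documents not shown.

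Part of this stands, and it rules out several stronger readings that a reader might draw:

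- **That data source is fully confounded with arm.** It is not. The two sources are joined by *or*, and intervention patients may have professional entries too. Only the automatic record is arm-specific.
- **That controls are cut off at about week 4.** No such rule is stated, and the 6-month visit may capture later use. On that reading, with 8 true weeks and 25%, 50% or 75% of controls cut at 4, the recorded control mean is 8(1 − s) + 4s = 7, 6 or 5 weeks, a false benefit of 1 to 3 weeks. Those shares have no basis in the document and assume that the 6-month visit adds nothing.
- **That the result must favour the chat-bot.** Its messages taper after the quit date, patients choose the timing and frequency of proactive contacts, and the Cost-utility section anticipates avoided visits. Patients who stop using the chat-bot while still on medication could be under-recorded.

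What does not stand is the appeal to condensation. The article does state the definition and both sources. The fault lies in what that definition permits, not in an omitted detail.

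**Conclusion.** The point holds as a weakness in the definition of a secondary outcome. As written, adherence may be ascertained through an instrument that only one arm has. No rule sets precedence between sources, and nothing requires a measure common to both arms. The comparison is therefore open to differential ascertainment. The likelier direction favours the chat-bot, because its contacts are denser and run to six months while control visits after one month are opportunistic. Neither direction nor size can be determined from the document.

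The figures above, from zero to about 1.5 weeks, rest on assumed use and on assumed shares without a later record. They show only that modest gaps in recording can matter with 230 per arm. A reader might infer that the adherence objective cannot be answered at all. The document does not support that, since a visit common to both arms already exists and could supply the measure. The primary outcome is unaffected.

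**What to change.** State in Adherence to treatment that the analysed variable is weeks of prescribed medication taken, asked with the same question in both arms at the existing 6-month data visit. Use chat-bot logs and interim visit entries descriptively or in a sensitivity analysis, labelled as such. If the comparison is restricted to patients with a prescription, report the proportion prescribed by arm beside it. Scoring patients without a prescription as 0 weeks would mix prescribing with adherence; that is a separate choice and is not needed for this fix.

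The cost is one DCN item, with no new visit and no change to treatment. The downside is recall error over six months. It may not be exactly equal between arms, because patients are unmasked and the chat-bot reminds one arm about medication. The change does remove the arm-specific instrument and the arm-specific timing.

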#### Explanative and adjusting variables

Patient-related socio-demographic variables (first level): 1) age (years); 2) gender (M/W); 3) socio-economic status (monthly income expressed as a multiple of the minimum wage); 4) educational level (no education/primary education/secondary education/university education); 5) nationality; 6) number of cigarettes/day; 7) number of previous attempts to cease smoking; 8) basal co-oximetry in exhaled air (ppm); 9) quit date; 10) level of nicotine dependence (brief form of Fageström Test); 11) continuous cannabis use (defined as at least once per week for the last month).

Healthcare centers and healthcare professionals (second level): 1) gender (M/W); 2) age (years); 3) professional category (medicine, nursing); 4) graduation year; 5) average workload (measured as the average daily consultations per health worker during the year prior to the trial).

### Statistical analysis

The results will be presented in accordance with the guidelines by the CONSORT declaration [23].

#### Description of basal characteristic

A descriptive analysis of the demographic and basal characteristics of subjects in both groups will be conducted: quantitative variables will be described by their measures of central tendency (mean or median in the case of asymmetric distributions) and their dispersion (standard deviation or interquartile range for normal or non-normal distributions, respectively). Qualitative variables will be described by their proportions with their confidence intervals set at 95% (CI 95%).

#### Basal comparison

Intergroup differences will be analyzed using statistical tests for independent samples (Student’s t-test or chi-squared test), whereas a test for related samples (repeated measures ANOVA) will be employed for differences within each group and across visits.

#### Main effectiveness analysis

Intergroup differences in the continuous abstinence rates at 6 months (main variable) will be analyzed with their CI 95%. Bivariate analysis: a Student’s t-test, or the Mann-Whitney U-test in case the hypothesis of data normality is rejected, will be used to compare the outcome between groups in the case of quantitative variables. For qualitative variables, either Pearson’s chi-squared test or Fisher’s exact test, when applicable, will be used. After adjusting for possible confounding factors, the odds ratio of the association will be calculated using a logistic regression model where the dependent variable will be the continuous abstinence (yes/no) and the independent variables will be patient-related variables and the study group. In all cases, statistical significance will be set at *p* < 0.05. Gained QALYs will be estimated at a population level with their relevant CI 95% via parametric analysis methods and bootstrap techniques. Cost-utility ratio: this aim is exploratory (there is no specific design for it). The cost-utility ratio will be calculated dividing the overall cost by the sum of potential gains expressed in QALYs. For normally distributed data, a multivariate sensitivity analysis will be conducted, making the costs fluctuate within the constructed range of uncertainty. For the same distribution, we will also make the benefits (QALYs) fluctuate within the CI 95%. In all cases, the analysis will be for intention-to-treat. The number of withdrawals, losses to follow-up, and subjects not complying with the protocol will be recorded together with the relevant reasons. Losses to follow-up will be considered as smokers in the analysis [24]. A participant will be considered lost to follow-up after missing two appointments, failing to be contacted by phone in at least two occasions, and having no registered explanation for it. Missing information on professionals and/or patients will be replaced using values from the baseline data.

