#### Sample size

The sample size was calculated based on the outcome of a clinical trial recently conducted of usual clinical care in Madrid public health system that employs a similar definition of continuous abstinence as our study [5]. It detected an abstinence rate of 9.6% at 6 months in the control group. We estimate that the intervention to be assessed will double this fig [13, 14]..

Based on these data, and considering a type I error of 5% and a power of 80%, the required number of patients will be 418. After estimating 10% of losses to follow-up, the required sample size is 460 smokers (230 in each group).

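### EQ-5D-5L is left to an unadjusted t-test or Mann-Whitney test; a baseline-adjusted mean difference would be more precise and would match the quantity used for QALYs

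*Protocol article*

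**What the plan says.** The protocol article lists quality of life on the EQ-5D-5L as a secondary objective, worded as an improvement compared with usual practice (Secondary objectives). The variables section states: "Two visits have been defined for data collection of patients: basal and at 6 months".

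Three places bear on how these data are analysed:

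- **Main effectiveness analysis.** Quantitative outcomes are compared between groups by Student's t-test, "or the Mann-Whitney U-test in case the hypothesis of data normality is rejected". The only model with covariates is the logistic regression for abstinence.
- **Basal comparison.** After the tests for intergroup differences, "a test for related samples (repeated measures ANOVA) will be employed for differences within each group and across visits".
- **Explanative and adjusting variables.** Eleven patient variables are listed. Baseline EQ-5D-5L is not one of them.

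Under Secondary outcome variables, QALYs are built from the between-group difference in utility at 6 months. Main effectiveness analysis gives them a 95% CI by parametric and bootstrap methods. The Discussion calls quality of life not confirmatory and expects limited change, but keeps it because "intergroup differences can be detected even if they are not strongly significant".

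**The concern.** Comparing improvement between arms calls for an analysis that uses the baseline value and also contrasts the arms. No analysis stated for EQ-5D-5L clearly does both. The between-group test has no covariates, and the repeated measures ANOVA uses the baseline but works inside each arm.

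Three things are at stake:

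- **Precision** is lost on an effect that the article itself expects to be small.
- **Chance imbalance** in baseline utility carries partly into the 6-month difference and so into the QALYs. The article then holds the 6-month utilities constant for one year.
- **The quantity tested can change.** Utility scores are bounded and often skewed, so a normality test may well reject at this sample size. The rule then selects a rank test, which does not test a difference in means, whereas QALYs need the mean difference.

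**Working it through.** **The plan's own figure.** The article states "It detected an abstinence rate of 9.6% at 6 months in the control group" and "We estimate that the intervention to be assessed will double this fig", so the rates are 9.6% and 19.2%. With two-sided alpha 0.05 and power 0.80:

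n per arm = [1.96 × √(2 × 0.144 × 0.856) + 0.8416 × √(0.096 × 0.904 + 0.192 × 0.808)]² / 0.096²
= (0.973 + 0.414)² / 0.009216 ≈ 208.8, rounded up to 209.

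Two arms give 418, which agrees with "the required number of patients will be 418". This figure concerns abstinence only. The article gives no SD, correlation or power for EQ-5D-5L. I use 209 per arm as the number with 6-month data.

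**Precision.** Let r be the correlation between baseline and 6-month values (assumed, since it is not in the document). ANCOVA multiplies the variance of the arm difference by 1 − r². The detectable difference at 80% power, in SD units, is (1.96 + 0.8416) × √(2(1 − r²)/209).

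| r (assumed) | 1 − r² | Equivalent extra patients, 1/(1 − r²) − 1 | Detectable difference (SD) | Power for an assumed 0.2 SD |
|---|---|---|---|---|
| unadjusted | 1 | – | 0.274 | 53% |
| 0.3 | 0.91 | 10% | 0.261 | 57% |
| 0.5 | 0.75 | 33% | 0.237 | 66% |
| 0.7 | 0.51 | 96% | 0.196 | 82% |

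**Chance imbalance.** The 95% range of the baseline utility difference is ±1.96 × SD × √(2/209). For assumed SDs of 0.10, 0.15 and 0.20 this is ±0.019, ±0.029 and ±0.038. With similar SDs at both visits, about r times the imbalance carries into the unadjusted 6-month difference. At r = 0.5 that is about ±0.010 to ±0.019.

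**The normality switch.** This simulation uses assumed shapes. In one arm 60% score 1 and the rest score 1 minus a gamma variable (shape 2, scale 0.10). In the other 50% score 1 and the rest score 1 minus a gamma variable (shape 2, scale 0.08). The means are equal: 1 − 0.4 × 0.20 = 1 − 0.5 × 0.16 = 0.92. With 209 per arm and 4,000 runs:

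- Shapiro-Wilk, applied to the first arm, rejected normality in 100% of runs, so the stated rule would choose Mann-Whitney.
- Mann-Whitney rejected in 25.5% of runs although the means were equal; the t-test rejected in 4.6%.
- With both arms drawn from the first, skewed distribution, the t-test rejected in 5.2%. The switch is not needed to protect the error rate at this sample size.

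The 25.5% shows what can happen when shapes differ. It is not a forecast for this trial.

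**The case against.** **EQ-5D-5L is not named in the sentence.** The rule is generic for quantitative variables. That is true, and the reading rests on elimination: no other between-group test is offered for these scores.

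**The test might be of change scores.** The objective speaks of improvement, and the Discussion of changes in quality of life, so a between-arm test of change would fit and would use the baseline. The article does not say this. If it were meant, the variance factor with equal SDs at both visits would be 2(1 − r): 1.4, 1.0 and 0.6 at r = 0.3, 0.5 and 0.7. ANCOVA gives 0.91, 0.75 and 0.51, so it remains the better choice.

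**The QALY estimate has its own method.** A reader might infer that the rank test produces the QALY figure or makes it wrong. It does not, because the QALY interval comes from parametric and bootstrap methods. What stands is that the quality-of-life p-value and the QALY estimate can address different quantities.

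**Within-arm tests as evidence.** A reader might infer that the trial will claim an effect because change is significant in one arm and not in the other. Nothing in the article plans that, and a between-group comparison is stated. The risk is one of interpretation only.

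**The stakes are low.** Quality of life is not confirmatory and the cost-utility aim is called exploratory. This stands and limits the severity.

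**Conclusion.** The point holds in a limited form. The only between-group method stated for quantitative outcomes is unadjusted and switches on a normality test, and no stated analysis adjusts the 6-month EQ-5D-5L comparison for baseline. This is a method the article fixes, so it is not a detail left to an unseen analysis plan.

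The cost is precision, exposure to chance baseline imbalance, and a possible mismatch between the p-value and the mean difference used for QALYs. A reader might infer bias, but under randomisation the unadjusted comparison is unbiased on average. A reader might also take a large gain from adjustment as given. The gain is equivalent to about 10% more patients at r = 0.3 and 96% at r = 0.7, and the document offers nothing to choose within that range.

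The outcome is secondary and not confirmatory, and the abstinence analysis is untouched. Severity is modest, and the change is worth making because it is nearly free.

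**What to change.** - For 6-month EQ-5D-5L utility and VAS, specify a linear model (ANCOVA) with study group and the baseline value of the same measure. Report the adjusted mean difference with a robust or bootstrap 95% CI. Remove the normality pre-test and the switch to Mann-Whitney for these outcomes.
- Use the same baseline-adjusted utility difference to construct the QALYs. The bootstrap already planned for them can be kept.
- State that the within-group repeated measures ANOVA is descriptive and is not evidence of an intervention effect.
- Confirm that EQ-5D-5L utility and VAS are recorded at the baseline visit, and add them to the listed baseline variables.

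If the baseline questionnaire is collected, as the two data visits imply, the cost is a change of wording only. If it is not, it would have to be added to the baseline visit.

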**Methods:**

Design: Randomized, controlled, multicentric, pragmatic clinical trial, with a 6-month follow-up. Setting: Healthcare centers in the public healthcare system of the Community of Madrid (Madrid Regional Health Service). Participants: Smokers > 18 years of age who attend a healthcare center and accept help to quit smoking in the following month. *N* = 460 smokers (230 per arm) who will be recruited prior to randomization. Intervention group: use of a chat-bot with evidence-based contents to help quit smoking. Control group: Usual treatment (according to the protocol for tobacco cessation by the Madrid Regional Health Service Main variable: Continuous nicotine withdrawal with chemical validation (carbon monoxide in exhaled air). Intention-to-treat analysis. Difference between groups in continuous abstinence rates at 6 months with their corresponding 95% confidence interval. A logistic regression model will be built to adjust for confounding factors. Results: First expected results in January 2020.

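### The main measure is a difference in abstinence rates, but the only adjusted result named is a covariate-conditional odds ratio, which is on another scale and adds no precision to that difference

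*Protocol article*

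**What the plan says.** Three places in the protocol article bear on this.

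- **Main measure.** The abstract (Methods) gives it as "Difference between groups in continuous abstinence rates at 6 months with their corresponding 95% confidence interval". The section Main effectiveness analysis repeats it: "Intergroup differences in the continuous abstinence rates at 6 months (main variable) will be analyzed with their CI 95"%. No adjustment is described for this difference.
- **Planning effect.** The Sample size section takes its control rate from an earlier trial of usual care in Madrid: "It detected an abstinence rate of 9.6% at 6 months in the control group". It then says "We estimate that the intervention to be assessed will double this fig". The target is therefore a ratio of rates of 2.
- **Adjusted analysis.** Main effectiveness analysis then states: "After adjusting for possible confounding factors, the odds ratio of the association will be calculated using a logistic regression model". In that model "the independent variables will be patient-related variables and the study group", so the odds ratio is conditional on those variables. The word conditional is mine, but it follows from the model.

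Nothing in the article turns the fitted model back into a difference or a ratio of rates.

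**The concern.** Abstinence at the planned rates is not rare enough for an odds ratio to stand in for a rate ratio. An odds ratio from a model with prognostic covariates also lies further from 1 than the unadjusted one when there is a true effect, even if the arms are perfectly balanced (non-collapsibility). The adjusted result therefore cannot be set directly beside the main difference, the planned doubling or the risk ratios cited in the Background. It will tend to look larger than the doubling.

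The second loss is of information. The section on explanatory and adjusting variables lists nicotine dependence, cigarettes per day, baseline carbon monoxide and previous quit attempts. These could sharpen the rate difference, but as written they feed only the odds ratio.

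**Working it through.** **Inputs.** From the Sample size section: control rate p1 = 0.096; doubled rate p2 = 0.192; "considering a type I error of 5% and a power of 80"%; "the required number of patients will be 418"; 460 after losses, 230 per arm. From Main effectiveness analysis: losses count as smokers, so all 460 enter. I take the planned rates as holding in all 460. The documents do not say how prognostic the covariates are, so I assume a normal prognostic score with SD s on the log-odds scale and show a range.

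**1. The plan's own figure.** Two-sided comparison of two proportions, pooled variance, no continuity correction, with p̄ = 0.144:

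n per arm = [1.960·√(2 × 0.144 × 0.856) + 0.842·√(0.096 × 0.904 + 0.192 × 0.808)]² / 0.096² = 208.8, so 209.

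Two arms give 418, an exact match. 418 × 1.10 = 460.

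**2. Scales at the planned effect** (no assumption beyond the two rates).

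- Difference: 0.192 − 0.096 = 9.6 points.
- Rate ratio: 0.192/0.096 = 2.00.
- Odds ratio: (0.192/0.808)/(0.096/0.904) = 0.2376/0.1062 = 2.24.
- Conversely, an unadjusted odds ratio of exactly 2.0 means odds of 2 × 0.1062 = 0.2124. That is a rate of 0.2124/1.2124 = 17.5%, and a rate ratio of 0.175/0.096 = 1.82.

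**3. Conditional odds ratio.** Take logit P = a + b·arm + score, with score ~ N(0, s²). Solve for a and b so that the average probabilities are 9.6% and 19.2%. The conditional odds ratio is exp(b).

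**4. Precision of the rate difference at N = 460.** Let m0 and m1 be a patient's probabilities under control and chat-bot.

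- Unadjusted: V = 2[p1(1 − p1) + p2(1 − p2)] = 2 × 0.24192 = 0.48384. SE = √(0.48384/460) = 0.0324, and the 95% half-width is 1.96 × 0.0324 = 6.4 points. At the planned effect the interval is 3.2 to 16.0 points.
- Standardised from the logistic model (large sample, model correct): V = E[2·m1(1 − m1) + 2·m0(1 − m0)] + Var(m1 − m0).
- Approximate power: Φ(0.096/SE − 1.96).

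| Assumed s | Conditional odds ratio | Variance ratio | SE | Half-width (points) | Power |
|---|---|---|---|---|---|
| 0 (unadjusted) | 2.24 | 1.00 | 0.0324 | 6.4 | 84% |
| 0.5 | 2.29 | 0.97 | 0.0319 | 6.3 | 85% |
| 1.0 | 2.47 | 0.89 | 0.0306 | 6.0 | 88% |
| 1.5 | 2.79 | 0.79 | 0.0288 | 5.7 | 91% |

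**5. What many terms cost.** The expected number of abstainers is 230 × (0.096 + 0.192) = 66. The article lists 11 patient variables, among them nationality and a four-level education variable. In simulations of 460 patients at the planned rates, a 14-term model (the count is an assumption) gave variance ratios of about 1.00, 0.93 and 0.84 at s = 0.5, 1.0 and 1.5. The gain at the weak end is gone.

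**The case against.** The best defence is that nothing here is inconsistent. The main measure is named and is estimated on all randomised patients. It agrees with the sample-size method, which reproduces as an unadjusted comparison of two proportions. A supportive adjusted analysis on another scale is ordinary practice. Readers can check the doubling from the two arm rates. Standardisation is a refinement that a condensed article may leave to the analysis plan, and naming an odds ratio does not exclude other summaries. The precision gain rests on a prognostic strength that the documents do not give.

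Much of this stands, and it rules out three stronger readings.

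- A reader might infer that the main result is biased or the trial wrongly sized. Neither follows. Randomisation makes the unadjusted difference valid, 418 reproduces, and with no true effect the odds ratio is not inflated.
- A reader might infer that the plan takes a shift between crude and adjusted odds ratios as evidence of confounding. The article says only that possible confounders will be adjusted for. It sets no such comparison and no change-in-estimate rule.
- A reader might infer that the interval for the difference is certainly wider than the data allow. That depends on how prognostic the covariates are and how many are entered. With many weak terms there is nothing to gain.

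What does not stand is that this is only missing detail. The article makes a positive choice of effect measure for the adjusted result under its main effectiveness heading. That choice does not match the scale on which it defines and plans the effect.

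**Conclusion.** The point holds as one of comparability and modest efficiency. At the planned doubling the odds ratio is 2.24 before adjustment, which needs only the document's own rates. It is about 2.3 to 2.8 after conditioning on covariates, for an assumed prognostic SD of 0.5 to 1.5. An odds ratio of 2.0 would be easy to read as the doubling, although unadjusted it means a rate ratio of 1.82.

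As specified, the adjustment does nothing for the interval of the main measure. Standardising the same model would lower the variance by about 3% to 21% with few covariates. Those are large-sample figures for a correct model; the lower end is small enough to vanish in practice, and a long covariate list brings it to nil. The change is worth making because it is nearly free and puts the adjusted result on the trial's own scale.

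**What to change.** Keep the unadjusted difference in abstinence rates with its 95% confidence interval as it is. Add one sentence to the analysis:

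- Fit the planned logistic model with study group and a few prespecified predictors measured before randomisation, for example dependence, cigarettes per day, baseline carbon monoxide and previous attempts.
- For every randomised patient, predict the probability of abstinence under each arm and average over all patients.
- Report the resulting difference in rates and the rate ratio, with 95% confidence intervals by the delta method or bootstrap, beside the unadjusted difference.
- Give the adjusted odds ratio as supplementary, labelled as conditional on the covariates.

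The covariate set should be short and named in advance, for the reason shown in step 5. The cost is a few lines of code and reliance on that prespecified set. It needs no new data, visits or patients.
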